### Intervention: the breast cancer care programme including ultra short stay

The intervention in this study concerns the comprehensive care programme for breast cancer surgery in ultra short stay (= ambulatory/24 hours stay setting). The key figures in the programme are the multidisciplinary team, the breast nurse, and the patient.

Traditionally, the surgeon has been the specialist who analyses the type of breast pathology presented. Preventive procedures, early diagnosis of non-palpable lesions, breast conserving therapy, and lymph node sparing therapy have raised possibilities to reduce the burden of breast (cancer) surgery. The role of the breast nurse was introduced to improve patient counselling. Through these developments, diagnosis and treatment of breast pathology have gained a more multidisciplinary character. A decrease in the burden of surgery may limit the need for hospital-based supportive care. Similarly, this leads to a demand for strict coordination of the different steps and disciplines involved. Moreover, responsibilities for aspects of care need to be reallocated to other persons: from hospital- based supportive caregiver towards informal caregiver, from clinician to nurse specialist, from in house nursing staff to outpatient nursing staff, from hospital-based nursing staff to home care nursing staff etc.

While the clinician's activities are limited to solving medical problems, the breast nurse performs all coordinating tasks to create a programme that runs smoothly.

The patient is the key figure in the process. In a one-hour consultation, following the preoperative diagnosis, the patient is informed by the breast nurse about all aspects of surgery (preparation, day of surgery, medication etc.). A checklist is used for this consultation and all oral information is supported by written information. Parts of this information (e.g. information on home care nursing and what to do in case of problems) are repeated on the morning of surgery, and at the moment of discharge.

### Implementation strategy

The first step in the implementation process concerns the assessment of the guideline recommendations by consensus among experts, who define the complete set of recommendations (n = 29) as well as a set of key recommendations (Table 1).

**Table 1 T1:** Key recommendations of the study guideline to enable ultra short stay for breast cancer surgery. The complete guideline contains 29 recommendations. The participating breast nurses and surgeons from the study groups rated all recommendations and decided upon which recommendations would be defined as 'key' recommendations.

• The treatment of all breast cancer patients is planned in a weekly multidisciplinary meeting.
• The interval between referral and first visit to the breast unit is 5 working days or less.
• The interval between diagnostic tests and informing patients about their results is 5 working days or less.
• The interval between the decision to operate and surgery is 15 working days or less.
• The number of preoperative hospital visits is minimised.
• The general practitioner is informed about diagnosis, treatment plan and potential side-effects prior to surgery.
• Patients planned for day care treatment are postoperatively given the choice between continuation of admission and discharge.
• Information given to patients about discharge is supported by written information.
• Decisions on patient discharge are based on clear guidelines.
• Specialised home care* for patients in the period following surgery is facilitated.
• The breast nurse stays in contact with the patient during the postoperative period.
• At least one night of hospital admission is planned for patients
with co-morbidity and/or insufficient postoperative supervision.
• The breast nurse informs the patient about the need for informal care in the home situation.

A so-called diagnostic analysis assesses the usual care, and explores factors that impede or facilitate the bridging of the gap between usual care and the programme to be implemented. Information for the diagnostics analysis will be retrieved from interviews during outreach visits, meetings, and telephone and e-mail conferences. The results of the assessment of usual care in the participating hospitals are compared to the standards of the innovative care programme. Information on perceived barriers and facilitators for implementation of the ultra short stay programme will be collected during outreach visits to the hospitals. These visits will be conducted in the recruitment and preparation phase. They will be aimed at preparation of the actual implementation and listing of the barriers and facilitators that were perceived by the participants for implementation of the care programme. This set of barriers and facilitators will be described on different levels: study guideline, care provider, patient, colleague, organisation, and financial resources and reimbursement[23].

Subsequently, a hospital-specific strategy is applied to implement a hospital-tailored version of the comprehensive care programme. This strategy is aimed at overcoming the barriers. Multi-faceted implementation strategies are used, providing insight, inducing change and acceptance, and feedback to maintain changes. These strategies are based on several components: 1) The promise that each early adopter makes to the project leader ([name]) to appoint a breast nurse fully available for coordination for the programme; 2) High-frequency outreach visits and study group meetings representing all disciplines involved in breast cancer care, provide the forum in which all steps for implementation are prepared, and issues are discussed and resolved. This local working party is also responsible for the communication of progress of implementation and of the findings within the hospital, to patients, and to other involved parties.; 3) The care process is measured through indicators mentioned in the Case Record Forms that are scored within the hospital, followed by feedback on performance by the researchers.

### Main indicators (Table 2)

**Table 2 T2:** Main indicators of the MaDO study.

*Outcome indicators*
• Final type of admission
• Readmission rate
• Complication rate
• Quality of care from the patients' perspective
• Cost-effectiveness of the ultra short stay programme
• Cost-effectiveness of the implementation strategy

*Process indicators*

• Involvement of home care nursing
• Performance of professionals according to the protocol
• Reasons why patients were not treated according to ultra short stay protocol

#### Measurements and timing of measurements (Figure 1)

**Figure 1 F1:**
[figure not shown]
**Overview patient questionnaires**. Overview of the type of questionnaires that are offered to patients and the time at which these questionnaires should be filled out.

- Information on the achievement of the targets of the implementation strategy is collected through Case Record Forms.

- Quality of care is measured from the patient's perspective through the QUOTE-breast cancer, a questionnaire that was developed by and for breast cancer patients and concerns those aspects that breast cancer patients perceive as most important when assessing quality of care[24,25]. The QUOTE-breast cancer questionnaire is filled out six weeks after surgery.

- Information on the performance of professionals is gained through Case Record Forms. The performance indicators have been developed by means of a consensus procedure in the uhM project group.

- Information on societal costs are retrieved from hospital information systems and through a prospective cost book that is filled out by patients during six weeks from the moment of discharge. The day before surgery, patients are asked to fill out a retrospective cost book to assess the patients' health-care related costs for a period of two weeks prior to surgery.

- Patients fill out EuroQol questionnaires at baseline (one day before surgery) and at 24 hours, one week and six weeks after surgery.

When patients sign informed consent and receive the questionnaires, a stamped envelope is given to them which can be used to return the set of questionnaires.

Programme cost-effectiveness (as compared to care as usual) consists of the two components costs and effectiveness, and is expressed as incremental costs per Quality Adjusted Life Year (QALY) of the ultra short stay programme versus care as usual. Incremental costs are expressed as the difference in costs between the ultra short stay programme and care as usual. Costs are calculated by multiplying the volumes with the appropriate cost prices. Information on (societal) costs are retrieved from hospital information systems and through a prospective cost book that is filled out by patients during six weeks from the moment of discharge. Effectiveness of the programme is determined through the measurement of safety, (number of complications, number of visits to the emergency unit, number of re-admissions etc.; information gained from the Case Record Forms) and generic health-related Quality of Life. Generic health-related Quality of Life is recorded through the EuroQol-5D (EQ-5D)[26], which is completed at baseline, 24-hours after surgery, 1 week after surgery and 6 weeks after surgery. QALYs will be determined in two ways; from a societal perspective using the Dolan score, and from an individual perspective using the VAS score of the EuroQol. The multiple imputation method will be used for missing data analysis[27].

- Policy cost-effectiveness of implementation of the ultra short stay programme versus 'doing nothing' is expressed as incremental costs per Quality Adjusted Life Year (QALY). Costs of the implementation strategy is measured through cost forms that participants in the study groups fill out, through scoring by a researcher ([name]) of all other costs (e.g. times, materials, travel costs) in a data sheet. Effectiveness of the implementation strategy is measured through Case Record Forms containing treatment information. More details on programme cost-effectiveness and policy cost-effectiveness can be found in the section 'Economic evaluation'.

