### Programme cost-effectiveness

The time horizon of six weeks seems appropriate as patients may receive additional treatment after surgery (e.g. radiotherapy, chemotherapy or hormone replacement therapy). Therefore, we expect that only short-term quality-of-life effects and costs can be attributed to the ultra short stay programme. Cost analysis includes health care costs and costs outside health care such as out-of-pocket costs or productivity costs due to reduction in paid work and/or domestic activities. Health care costs refer to hospital and other health care facilities costs. Hospital costs consist of personnel, material, capacity costs, and overhead, associated with the diagnosis, surgical treatment, hospital stay and follow-up. Other healthcare costs include costs of visits to the general practitioner, medication, home care etc. Health care costs are estimated by multiplying the resource utilization with the cost price per unit. Most of these costs are estimated by using existing resource registration systems and available cost prices through the financial departments of the participating centres. If true cost prices are not available in the participating centres, 1) existing cost prices of the uhM or 2) official directive prices are used[28]. Healthcare costs incurred outside the hospital and costs outside health care are partly estimated through a structured cost book that is kept by all participating breast cancer patients during the period of six weeks following discharge. Productivity losses due to absence from work are estimated through the friction cost method[28,29]. To perform the cost-effectiveness analysis, costs and effects of patients treated according to care as usual (before implementation) will be compared to costs and effects of patients treated according to the ultra short stay programme (after implementation).

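### Patient-reported costs are collected for six weeks from discharge but QALYs end six weeks after surgery, so the cost window moves with length of stay, which the programme is meant to change

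*Protocol article*

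**What the plan says.** Cost clock. Under Measurements and timing of measurements, the protocol article takes societal costs from hospital information systems and from "a prospective cost book that is filled out by patients during six weeks from the moment of discharge". The account of programme cost-effectiveness in the same section repeats this. The Programme cost-effectiveness section says again that the book is "kept by all participating breast cancer patients during the period of six weeks following discharge".

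Effect clock. The measurements section states: "Patients fill out EuroQol questionnaires at baseline (one day before surgery) and at 24 hours, one week and six weeks after surgery". The account of programme cost-effectiveness gives the same schedule for the EQ-5D, "which is completed at baseline, 24-hours after surgery, 1 week after surgery and 6 weeks after surgery".

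Horizon. The Programme cost-effectiveness section sets a single duration without a starting point: "The time horizon of six weeks seems appropriate as patients may receive additional treatment after surgery".

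Other cost sources. A second, "retrospective cost book to assess the patients' health-care related costs for a period of two weeks prior to surgery", is completed the day before surgery. Hospital costs are those "associated with the diagnosis, surgical treatment, hospital stay and follow-up", mostly from existing registration systems. Costs outside the hospital are said to come only partly from the cost book.

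The article contains no statement that cuts costs off at six weeks after surgery or that aligns the two clocks.

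**The concern.** The start of the cost book is tied to discharge, and earlier discharge is what the programme sets out to achieve. The position of the costed period relative to surgery therefore differs systematically between the two groups that the Programme cost-effectiveness section compares, while the QALY period does not.

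This has two consequences.

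- **Late overrun.** A patient who stays longer is followed for costs further beyond day 42. The protocol justifies the short horizon by pointing to additional treatment that may follow surgery. Usual-care cost books reach further into that later period.
- **Early gap.** The cost book does not cover surgery to discharge. Out-of-pocket costs and paid or domestic work lost on those days lie outside it for a patient still in hospital, and inside it for a patient already at home. The retrospective book does not fill the gap, because it covers the two weeks before surgery and only health-care-related costs.

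At stake is the incremental cost per QALY (objective 3) and the policy cost-effectiveness built on it (objective 4). Numerator and denominator refer to different periods, and the mismatch depends on the exposure.

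**Working it through.** No figure in the plan can be reproduced here. The six-week horizon is a stated duration, so the check is calendar arithmetic with surgery as day 0.

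**Inputs from the protocol article**

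- Cost book: 42 days from discharge (Measurements and timing; Programme cost-effectiveness).
- Last EQ-5D: day 42 after surgery (Measurements and timing).
- Stay in the programme: 0–1 day (Intervention section: ambulatory or 24-hour setting).
- Smallest pre-post change planned for: 30 percentage points (Sample size calculations).
- Change seen at the originating hospital: 84 − 13 = 71 percentage points (same section).

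**Assumption.** The usual-care stay in the four hospitals is not given. I take 2–10 days, the span of the two arms (2–4 and 5–10 days) of the early-discharge trials described in the Background.

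**Formulas**, with L the length of stay in days:

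1. The cost book covers day L to day L + 42. QALYs end at day 42.
2. Overrun past day 42 = L. Uncovered gap after surgery = L. The book lasts 42 days in every patient; only its position moves.
3. Per-patient shift between groups = L(usual) − L(programme).
4. Pre-post mean shift = share of patients changing × per-patient shift, taking the stay of all other patients as unchanged.

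**Results**

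| Usual stay (days) | Cost book ends | Per-patient shift against 0–1 day | % of 42 | Mean shift, 30 points change | % of 42 |
|---|---|---|---|---|---|
| 2 | day 44 | 1–2 days | 2.4–4.8 | 0.3–0.6 day | 0.7–1.4 |
| 5 | day 47 | 4–5 days | 9.5–11.9 | 1.2–1.5 days | 2.9–3.6 |
| 7 | day 49 | 6–7 days | 14.3–16.7 | 1.8–2.1 days | 4.3–5.0 |
| 10 | day 52 | 9–10 days | 21.4–23.8 | 2.7–3.0 days | 6.4–7.1 |

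A programme patient's book ends on day 42 (stay 0) or day 43 (stay 1). Worked example for a usual stay of 5 days against 1 day: 47 − 43 = 4 days; 4/42 = 9.5%; 0.30 × 4 = 1.2 days; 1.2/42 = 2.9%.

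Thirty points is the minimum the sample size assumes. With a 71-point change the mean shift runs from 0.71 × 1 = 0.71 day (1.7%) to 0.71 × 10 = 7.1 days (16.9%) over the same range of stays.

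**Direction.** For one patient, the error in patient-reported cost is

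(costs on the L days after day 42) − (non-hospital costs and lost work on the L days between surgery and discharge, unless another source supplies them).

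The first term inflates usual-care cost and the second deflates it. The sign depends on whether a day just after surgery costs more or less outside hospital than a day after week six. The protocol gives no figures for either.

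**After the fix.** If both windows start at surgery and end at day 42, the shift is 0 days at any length of stay.

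**The case against.** The strongest reply concerns size and does not dispute that the clocks differ.

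- **Length of stay.** A reader might take the 5–7 days in the Background as the usual stay and conclude that the window is off by 10–14% (4–6 days against a 1-day programme stay). The text does not support this. It describes a historical decline that continued down to day care, and the four hospitals were chosen as early adopters. The Discussion, arguing against randomising patients, speaks of a neighbour staying a day or two longer. That is not a baseline estimate either, but it shows that no particular gap is fixed. This objection stands, so the size has to be given as a range.
- **Dilution.** Any per-patient figure overstates the group contrast, because some baseline patients already go home early and some post-implementation patients stay longer. This stands. With 30 points changing, a 4–6 day gap averages 1.2–1.8 days, or 3–4% of 42.
- **Stay already costed.** The admission itself is costed from hospital systems, so the mismatch does not lose it. This stands, although the article gives no end date for those costs.
- **Admission-day losses.** A reader might infer that lost work during admission is recorded in one group only. The protocol says that outside costs are partly estimated from the cost book, so another source may recover some of it. None is named, so the gap is a risk and not an established loss.
- **Detail left to a fuller document.** Whether entries are dated, and how admission days are valued, may be settled elsewhere. This stands for those details. It does not cover the discharge start itself, which the article states three times as a rule.

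**Conclusion.** The point holds as a misalignment of the cost and effect windows that depends on exposure. The cost book is consistently tied to discharge, the EQ-5D is consistently tied to surgery, and length of stay is what the programme changes.

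On an assumed usual stay of 2–10 days against 0–1 day, the per-patient shift is 1–10 days (2–24% of 42). The pre-post mean shift is about 0.3–3.0 days (1–7%) if 30 percentage points of patients change, and larger if more do. Confidence in the mismatch is high. Confidence in its size is low until the baseline length of stay is known.

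It would be tempting to conclude that the design favours the programme, or that the cost-per-QALY result is invalid. The documents support neither: the two errors oppose each other, their net sign is unknown, and no monetary size can be derived. The severity is moderate. Objectives 3 and 4 are affected through patient-reported costs; the primary outcome is not.

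**What to change.** State that the six-week horizon starts on the day of surgery, and close both costs and effects at day 42 after surgery, in both measurement periods. There are two ways to do this.

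1. **Change the cost book.** Start it on the day of surgery, add a line for paid and domestic work days lost during admission, and end it at day 42 after surgery.
2. **If books are already in use.** Have entries dated, truncate at day 42 after surgery in both periods, and add admission days to productivity loss from the recorded admission and discharge dates. Out-of-pocket costs during admission cannot be rebuilt from dates, so report that residual gap. Entries without dates cannot be realigned later, so dating should be settled before collection goes further.

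Apply the same day-42 cut-off to costs drawn from hospital systems, and report length of stay by period so that readers can judge what the alignment changed.

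The cost is a revised cost-book instruction or a truncation rule in the analysis. No extra visits, questionnaires or patients are needed.

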### Time schedule for the study

The study lasts three years. The first year of the study will be spent on the analysis of the breast cancer care processes in the different hospitals and the development of the measurement instruments. The following six months are used for baseline measurements, and preparation of the implementation of the new programme by the members of the local study groups. Recruitment of patients will be performed by breast nurses and advanced practice nurses working at the breast units. Then, six months are used for implementation and running of the actual programme, followed by six months of measurements 'after implementation'.

### Statistical analyses

Intention to treat will be used for data analyses, and analyses will be performed using the SPSS package, version 12.0.1 ^® ^for Windows (SPSS INC 1989–2003). P values < 0.05 will be defined as statistically significant. The pre and post comparison of the interval scaled outcome variables will be analysed with a multivariate linear regression model. Apart from the independent variable hospital, other independent variables included in this model are type of surgery, age, informal care at home, involvement of home care nursing and starting time of surgery. Furthermore, correlation of data within a hospital are accounted for by clustered data analysis.

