## Methods/Design

### Study design

The MaDO study is a multi-centre pre-post uncontrolled prospective study and involves breast cancer patients who are operated on with curative intent. Both pre and post- measurements last six months with an implementation period of six months in between.

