### Informed consent

Eligible patients are informed about the study by the breast nurse during a consultation separate from the consultation in which they are informed about the diagnosis breast cancer. Patients are given an informed consent form by the breast nurse when they are informed about the study, and they are asked to return the signed informed consent within a week. The informed consent regards consent to being asked to complete questionnaires with the aim to evaluate the cost-effectiveness of (the implementation of) the innovative care programme.

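### Baseline EQ-5D is collected in both periods but is not among the covariates for the pre/post comparison, so a systematic difference in starting health would be read as a programme effect on quality of life and QALYs

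*Protocol article*

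**What the plan says.** The Study design section describes a "multi-centre pre-post uncontrolled prospective study". Each measurement period lasts six months, with six months of implementation between them. The abstract labels the design controlled, but the Discussion explains why there is no concurrent control group.

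Statistical analyses gives one model: "The pre and post comparison of the interval scaled outcome variables will be analysed with a multivariate linear regression model". Hospital is one covariate, and the section then says: "other independent variables included in this model are type of surgery, age, informal care at home, involvement of home care nursing and starting time of" (the last item is when the operation begins). The list is stated outright, not as examples.

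Measurements and timing of measurements says: "Patients fill out EuroQol questionnaires at baseline (one day before surgery) and at 24 hours, one week and six weeks after surgery". The day before surgery, patients also "fill out a retrospective cost book to assess the patients' health-care related costs for a period of two weeks prior to surgery". These forms go to patients who consent: "The informed consent regards consent to being asked to complete questionnaires".

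The cost-effectiveness text under Measurements and the Programme cost-effectiveness section define incremental costs and effects as the difference between patients before and after implementation. Neither states an adjustment for baseline. The Discussion accepts that a pre-post design cannot exclude ongoing changes in health care, and says this will be weighed when conclusions are drawn.

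**The concern.** Nothing in this design balances starting health between the two cohorts. Of the variables to be collected, EQ-5D on the day before surgery measures starting health most directly, yet it is missing from a covariate list detailed enough to include starting time of surgery.

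If post-period patients arrive in systematically better or worse health, that difference persists in their later scores and becomes part of the estimated programme effect. Using baseline as the first point of the QALY curve does not correct this, because that point carries almost no weight. At stake are the EQ-5D comparisons and the QALY denominator of the programme and policy cost-effectiveness ratios. Omitting a correlated baseline also gives wider confidence intervals than the collected data allow.

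**Working it through.** The plan gives no precision or power figure for EQ-5D or QALYs, so there is none to reproduce. Its 40 patients per hospital per period was derived for the primary outcome and is used here only for cohort size.

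**Inputs from the article**
- Cohort size: 4 hospitals × 40 = 160 per period, as a minimum.
- EQ-5D times: days −1, 1, 7 and 42.
- Period midpoints: months 3 and 15 from the start of baseline measurement, so 12 months apart.

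**Assumed inputs (not in the article)**
- Utility SD 0.15–0.25, equal at all times, so that slope equals correlation.
- Baseline-to-follow-up slope or correlation within 0.3–0.7, the same at every later assessment.
- Independent patients; the other covariates explain none of the baseline difference.

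**1. Weight of baseline in the QALY (trapezoid rule)**
- Intervals are 2, 6 and 35 days.
- Weights are 2/2 = 1, (2+6)/2 = 4, (6+35)/2 = 20.5 and 35/2 = 17.5, total 43 days.
- Shares are 2%, 9%, 48% and 41%. About 98% of the QALY comes from scores after surgery.

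**2. Carry-over of a 0.03 baseline difference**
- Formula: difference × slope × 42/365.
- Slope 0.3: 0.03 × 0.3 × 42/365 = 0.0010 QALY.
- Slope 0.6: 0.03 × 0.6 × 42/365 = 0.0021 QALY.
- Direct contribution of the baseline point: 0.03 × 1/365 = 0.00008.

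**3. Comparison with a true short-term gain**
- 0.05 × 7/365 = 0.0010 QALY; 0.10 × 7/365 = 0.0019 QALY.
- If a 0.05 gain instead lasted all six weeks, the carry-over would be 0.03 × 0.3/0.05 = 18% to 0.03 × 0.6/0.05 = 36% of it.

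**4. False-positive rate with a systematic baseline shift and no true effect**
- SE = SD × √(2/160). At SD 0.20 this is 0.0224 (0.017–0.028 over SD 0.15–0.25).
- For a shift of 0.05, bias in a follow-up score = correlation × 0.05, tested at two-sided 5%:

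| Correlation | Bias | Rejection rate |
|---|---|---|
| 0.3 | 0.015 | 10% |
| 0.5 | 0.025 | 20% |
| 0.7 | 0.035 | 35% |

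**5. Chance imbalance only**
- Overall rejection stays at 5%, because the SE already includes this variation.
- Given an observed imbalance as large as 1.96 SE, conditional rejection is 8%, 13% and 20% for correlations 0.3, 0.5 and 0.7.

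**6. Precision**
- Variance ratio after adjustment = 1 − r².
- r = 0.4: 1 − 0.16 = 0.84, a 16% cut. r = 0.6: 1 − 0.36 = 0.64, a 36% cut.
- Equivalent extra patients: 1/0.84 = 1.19 and 1/0.64 = 1.56, so 19–56%.

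**The case against.** The strongest reply is that this is a condensed article. One generic list serves all interval-scaled outcomes, including the QUOTE, which is measured once and has no baseline, so an outcome-specific term might not appear there. The economic sections name no regression, and baseline adjustment of QALYs could be in an analysis plan that is not shown. This has some force: that the regression governs QALYs is a natural reading but is not stated. It does not remove the point, because the article chose to state its covariates and no section adds baseline.

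The cohorts come from the same four hospitals under the same criteria, with age and type of surgery adjusted for, and the documents show no actual shift in starting health. That stands. The bias is a risk of the design, not an observed fact, and every magnitude above rests on assumed inputs.

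A reader might infer more than the documents support:
- **That chance differences between cohorts invalidate the test.** They do not; step 5 shows the overall error rate is kept.
- **That the expected quality-of-life effect is small.** The article says only that it is short-term.
- **That baseline is available for every consenting patient.** That is the intention; forms are self-completed and multiple imputation is planned.
- **That pre-surgery costs should be adjusted for in the same way.** The programme acts before surgery, through the nurse consultation, fewer pre-operative visits and a limit on the interval to surgery (Intervention section; Table 1). Costs in those two weeks may be changed by the programme or belong to the cost outcome, and adjusting for them could remove real savings.

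**Conclusion.** The point holds for the EQ-5D and QALY comparisons. The stated covariates omit a baseline that is already collected, in a design with nothing else to balance starting health. The valid grounds are systematic or calendar differences between cohorts and lost precision.

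Under the assumed slopes, a 0.03 baseline difference is worth about as much as a one-week utility gain of 0.05–0.10, so it could mask or reverse such a gain. It would be a minor share of a benefit lasting the full six weeks. The precision gain does not depend on any imbalance, only on the assumed correlation.

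The point does not reach the primary outcome (percentage treated in ultra short stay) or the QUOTE, and it does not support adjusting the main cost analysis. Baseline adjustment would also not remove trends that act after the baseline assessment. The change is worth making for secondary endpoints; the omission does not undermine the study.

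**What to change.** - In Statistical analyses, add baseline EQ-5D as a covariate for every follow-up EQ-5D and QALY comparison: the index for index-based outcomes, the VAS for VAS-based outcomes.
- State that the same adjustment applies to the QALY difference in the economic evaluation.
- Include baseline EQ-5D in the multiple imputation model.
- Report the estimate without baseline adjustment alongside.
- Use the two-week pre-surgery cost, if at all, only in a sensitivity analysis.

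The cost is analysis wording; no new data are needed. There is one small downside. The post-period baseline is taken after the pre-operative nurse consultation, so any programme effect on pre-operative well-being would be adjusted away. The estimate without baseline adjustment would show this.
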